### 3.2. Control Group

To match with the experimental group in terms of the intensity of activities and duration of the study, a sham Qigong exercise will be utilized. The sham Qigong instructor will be blinded to the study hypothesis to avoid a potential bias and minimize any influence on study outcomes. The sham Qigong exercise consists of the same mild body movements as the Qigong exercise. However, participants in the control group will not be taught abdominal breathing techniques with six healing sounds and meditation during the exercise. The format of Sham Qigong exercise program will be the same over the 12-week intervention. The control group will have group meetings separately from the experimental group, once per week in the first six weeks, and every other week the last six weeks. During group meetings, the sham Qigong instructor will assess the performance of each participant and discuss relevant issues that are the same topics for the experimental group meeting for about an hour. The same baseline, post-intervention, and 6-month follow-up assessments will be conducted. This group will be asked to practice the sham Qigong exercise twice a day at home and keep an exercise diary.

### 3.3. Adverse Events

Any adverse events will be immediately reported to the principal investigator and, if appropriate, to the Human Participants Committee per the University of Kansas Medical Center Human Participants Committee policies. The principal investigator will be notified immediately of chest pain, irregular pulse, fainting, shortness of breath, light headedness, dizziness, excessive sweating, slurred speech, blurred vision, leg swelling, falls, or any other adverse events.

## 4. Outcome Measures

### 4.1. Demographic and Clinical Information

Demographic information including age, date of birth, sex, race, occupation, highest level of education completed, and years at school from elementary. In addition, clinical information will be obtained including diagnosis, date of diagnosis, and current medications. Participants will be asked to report if there are any changes in medications during the study period.

### 4.2. Clinical Assessments

The following clinical questionnaires and neuropsychological tests, commonly used in research and clinical settings in individuals with PD, will be utilized to assess participants. Based on our previous trials, the total estimated time to complete the following clinical questionnaires is an hour.
Sleep quality will be measured using the Parkinson’s Disease Sleep Scale-2 (PDSS-2). This 15-item questionnaire addresses issues related to sleep quality, which has been shown to be reliable in identifying issues specific to PD [33]. A lower score indicates better sleep quality. The minimal clinically important difference (MCID) is the threshold of −3.44 points for detecting improvement or the threshold of 2.07 points for detecting worsening [34].Cognitive function will be assessed using standardized clinical testing methods. The Frontal Assessment Battery evaluates executive function including conceptualization, mental flexibility, programming, sensitivity to interference, inhibitory control, and environmental autonomy [35]. Its maximum score is 18. A higher score indicates better performance. The ten-point clock test will be used to evaluate cognitive deficits. In this test, participants will draw a round-faced clock with hands at ten past eleven. Scoring will be performed using the criteria by Manos and Wu (1994) [36]. The trail making test parts A and B will assess visual attention and task switching. In these tests, participants will connect a set of dots as quickly as possible. The completion time will be compared with normative data [37].Comprehensive non-motor symptoms in PD will be measured by the Parkinson’s Disease Non-Motor Symptom Questionnaire [38]. The assessment contains a total of 30 items including 10 domains (gastrointestinal tract symptoms, urinary tract symptoms, sexual function, cardiovascular symptoms, apathy/attention/memory, hallucinations/delusions, depression/anxiety/anhedonia, sleep/fatigue, pain, and miscellaneous (diplopia, weight loss, etc.)). A lower total score indicates milder PD symptoms.Fatigue level will be measured by the 16-item Parkinson Fatigue Scale, which has shown reasonably good reliability and validity in testing fatigue specific to PD [39]. Its maximum score is 90. A lower score indicates better symptoms.Anxiety and depression will be measured using the 20-item Geriatric Anxiety Inventory and 15-item Geriatric Depression Scale [40,41]. For both scales, a lower score indicates less anxiety or depression.The severity of PD motor and non-motor symptoms will be assessed by the Movement Disorder Society—Unified Parkinson’s Disease Rating Scale (UPDRS) [42]. This assessment consists of four parts including non-motor experiences of daily living (13 items), motor experiences of daily living (13 items), motor examination (18 items), and motor complications (6 items). A lower score indicates milder PD symptoms. The MCID is 2.5 points for detecting minimal improvement in the motor score and 4.3 points for observing minimal improvement in the total score [43].Quality of life will be evaluated using the 39-item Parkinson’s Disease Questionnaire [44]. This assessment covers eight dimensions, including mobility, activities of daily living, emotional well-being, stigma, social support, cognition, communication, and bodily discomfort. A lower score indicates better quality of life. The MCID of sub- and overall-scores suggested by Peto et al. (2001) will be utilized [45].

Of note, the UPDRS is a standard measure of PD severity, which includes measurements of motor impairment and non-motor symptoms in individuals with PD. However, the primary focus of the study is non-motor symptoms, thus the motor symptoms of UPDRS will only be used to describe clinical status of the participants. The results of the questionnaires will be manually entered into an encrypted database by a member of research team who is blinded to study participants and group assignments.

### 4.3. Serum Biomarkers

Venous blood samples will be collected from participants three times, baseline, post-intervention, and 6-month follow-up. At each timepoint about 30 mL of blood will be collected using the BD vacutainer^®^ blood collection tubes (Becton, Dickinson and Company, Franklin Lakes, NJ, USA; catalog number 367820). Blood draws will be performed by a registered nurse between 9 am and 11 am. After the blood draw, collected samples will be placed at room temperature for approximately 30 minutes for coagulation. Coagulated blood samples will be centrifuged at 1,000 × g at 4 °C for 10 min to separate serum from blood clot and cells. Collected serum will be immediately aliquoted and stored at −80 °C in a freezer until assaying.

When performing the assay, aliquoted samples will be thawed, gently vortexed, and processed to separate any precipitation by centrifugation at 14,000 × g at 4 °C. We will measure the levels of the following biomarkers by enzyme-linked immunosorbent assay (ELISA) using commercially available kits: IL-1β (RayBiotech, Norcross, GA, USA; detection range 3 pg/mL to 1000 pg/mL), IL-6 (RayBiotech, Norcross, GA, USA; detection range 3 pg/mL to 1,000 pg/mL), and TNF-α (ThermoFisher Scientific, Rockford, IL, USA; detection range 15.6 pg/mL to 1,000 pg/mL).

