Although it may be impossible to stop neurodegeneration in PD, many therapeutic approaches have been developed to alleviate symptoms in PD. Qigong is a mind-body exercise that has shown benefits on symptoms in PD. A study involving individuals with mild to moderate PD demonstrated a significant improvement in sleep quality [16]. In our feasibility study in a single-arm design (n = 7), a 6-week Qigong exercise program demonstrated an improvement in sleep quality measured by Parkinson’s Disease Sleep Scale-2 (PDSS-2), in which the results showed sub-scores of PDSS-2 were significantly improved or showed a trend of improvement including motor symptoms at night (*p* < 0.05) and disturbed sleep (*p* = 0.06) in individuals with PD [17]. Our recent pilot study, a randomized controlled trial (RCT), in individuals with PD showed a significant improvement in sleep quality, including PD symptoms at night (*p* < 0.05) and total PDSS-2 score (*p* < 0.001), after practicing the Qigong exercise for eight weeks (2-week training + 6-week Qigong exercise) [18].

The exact mechanism of Qigong exercise behind clinical improvements observed in patients with PD has not yet been completely understood. A possible mechanism of Qigong exercise may involve biological pathways related to neuroinflammation. The deep abdominal breathing may stimulate serotonin pathways by stimulating enterochromaffin cells that release serotonin [19] and interact with pro-inflammatory cytokines that contribute to neuroinflammation in the brain [20]. Our recent pilot study suggested potential benefits of Qigong exercise through changes in inflammation status, in which the results showed a significant decrease in serum level of TNF-α from 13.8 ± 0.6 to 12.3 ± 1.6 (*p* < 0.05) that was significantly correlated with changes in sleep quality and serum TNF-α level (R^2^ = 0.62) [18]. In various medical conditions, mind-body exercises such as Yoga, Tai Chi, and Qigong improved the immune system [21]. Particularly, past studies reported the benefits of Qigong exercise on immunological functions in healthy people [22] and individuals with cancers [23,24,25]. 

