## 2. Study Design and Aims

### 2.1. Study Design

We designed a double-blind RCT involving 60 individuals with PD (Figure 1). The participants will be randomly assigned to either an experimental (n = 30) or control (n = 30) group. Each group will have group exercise meetings (nine times in total; weekly meeting for first six weeks and then biweekly meetings for next six weeks) throughout the 12 weeks of the intervention period. Participants will be blinded to their group assignments until the end of the study. At baseline, all outcome measures and demographic variables including age, sex, ethnicity, years of education, disease duration, and medications will be collected. After the baseline assessments, participants in both groups will have a 12-week intervention period, including three weeks of training and nine weeks of exercise. The duration of the intervention will be longer than our two previous studies to provide more structured training sessions and longer intervention time [17,18]. During the training period, participants in the experimental group will learn the Qigong exercise, whereas those in the control group will learn the sham Qigong exercise. During the exercise period, participants will continue to practice what they will have learned during the training period. Throughout the 12-week intervention period, all participants will be asked to perform their assigned exercise (Qigong or sham Qigong exercise) twice a day at home, in the morning and evening, attend group meetings (weekly meeting for first six weeks and then biweekly meetings for next six weeks) and keep an exercise diary. The exercise diary includes daily checklists (morning exercise (yes/no), evening exercise (yes/no), and other exercise more than 0.5 h (yes/no)), subjective scales (sleep quality (1–5), fatigue level (0–10), and pain level (0–10)), and participant’s note for any unusual events. Within two weeks after the completion of the 12-week intervention, post-intervention assessments will be conducted, which are the same as the baseline assessments. The assessments will be completed again six months after the end of the intervention period.

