## 3. Intervention

### 3.1. Experimental Group

The experimental group will learn a specific type of Qigong exercise named ‘six healing sounds’ Qigong. The six healing sounds Qigong exercise consists of mild-body movements, meditation, and abdominal breathing along with uttering six healing sounds. The detailed instruction for the body movements and sounds can be found in Table 2. This form of exercise is chosen because it is appropriate for individuals with PD who may have reduced physical capacity since this exercise is easy to learn and safe to perform. The exercise mainly involves upper mild-body movements and can be performed in any position including standing (preferred), sitting, or lying down. Trained Qigong instructors will lead the 12-week intervention period throughout the study. The format of the Qigong exercise program will be the same over the 12-week intervention.

Participants will be instructed to practice the Qigong exercise at home twice a day in the morning after getting up and in the evening before going to bed. A Qigong exercise session usually takes between 15 and 20 minutes to perform. Participants will be asked to record their exercise performance and self-rated levels of pain, fatigue, sleep quality in a daily exercise diary throughout the study. Participants will have a group meeting every week for the first six weeks and every other week for the remaining six weeks. During group meetings, the Qigong instructor will assess the performance of each participant and discuss relevant issues for about an hour. Also, if a participant shows a sign of low adherence to the exercise, the instructor will provide a behavioral coaching to increase the adherence level based on the model of behavioral change [32]. After the completion of the 12-week intervention period, participants will be asked to continue practicing the Qigong exercise twice a day at home and keep an exercise diary. At the end of the 6-month follow-up, participants will return for a follow-up assessment, which is the same as the baseline and post-intervention assessments.

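### Practice after getting up and a 9 to 11 am draw window probably place both post-baseline blood samples, but never the baseline sample, after a same-day session, so any immediate cytokine effect would be mixed with a longer-lasting one

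*Protocol article*

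**What the plan says.** Sampling (section 4.3): "Venous blood samples will be collected from participants three times, baseline, post-intervention, and 6-month follow-up". "Blood draws will be performed by a registered nurse between 9 am and 11 am". The section sets no condition on practice before a draw.

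Practice (sections 2.1, 3.1 and 3.2): Qigong participants are to practise "twice a day in the morning after getting up and in the evening before going to bed", and "A Qigong exercise session usually takes between 15 and 20 minutes to perform". Section 2.1 gives both arms the same morning and evening schedule during the 12 weeks. It places baseline assessments before training and the post-intervention assessment in the two weeks that follow week 12. For the period after week 12, section 3.1 says of the Qigong arm that "participants will be asked to continue practicing the Qigong exercise twice a day at home". Section 3.2 also asks for sham practice twice daily, but does not say whether this runs beyond week 12.

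What separates the arms (sections 1 and 3.2): sham shares the body movements and leaves out abdominal breathing, the sounds and meditation. The introduction proposes breathing as the route to the cytokines: "The deep abdominal breathing may stimulate serotonin pathways by stimulating enterochromaffin cells that release serotonin".

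Use of the data (sections 2.2 and 5.2): Aim II compares the fall in IL-1β, IL-6 and TNF-α between arms. Aim III correlates cytokine changes with symptom changes across both arms. If there is no interaction, a repeated measures ANOVA examines time.

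**The concern.** Two stated rules combine in a way that neither shows alone. Holding the clock time constant is good practice for cytokines, but here it sets the draw shortly after the hour at which participants are told to exercise. Sampling conditions then differ systematically between baseline and both later visits.

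If one session shifts serum cytokines for a few hours, the measured change contains that shift as well as whatever 12 weeks of practice has built up. The shift could have either sign: an immediate rise could hide a longer-lasting fall, and an immediate fall could be read as a change in underlying inflammatory status. The data as scheduled could not tell these apart. The diary in section 2.1 records morning exercise as yes or no, without a clock time, so it would not supply the interval between practice and draw.

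**Working it through.** **1. The schedule, visit by visit, for a participant who follows the instructions**

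| Draw (9 to 11 am) | Qigong: session that morning? | Sham: session that morning? |
|---|---|---|
| Baseline | No; nothing has been taught yet | No |
| Post-intervention (within two weeks after week 12) | Likely; continued practice is requested (3.1) | Unclear; continuation after week 12 is not stated (3.2) |
| 6-month follow-up | Likely, for the same reason | Unclear, for the same reason |

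No post-baseline draw falls inside the 12 weeks for which section 2.1 explicitly gives both arms the same schedule.

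**2. What the analyses would then contain**

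Notation: L_Q and L_S are the longer-lasting changes in the two arms. M is an immediate effect of the shared movements, and B is the additional immediate effect of breathing, sounds and meditation. p_Q and p_S are the proportions who practised on the morning of the draw. At baseline every immediate term is zero.

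- Mean change, Qigong: L_Q + p_Q(M + B)
- Mean change, sham: L_S + p_S·M
- Contrast between arms: (L_Q − L_S) + p_Q·B + (p_Q − p_S)·M

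If both arms practise equally on draw mornings (p_Q = p_S), M cancels and p_Q·B remains. If sham participants have stopped, part of M remains too. The time effect within an arm keeps its whole immediate term. In Aim III an immediate shift identical for everyone would leave a correlation coefficient unchanged. It would enter so far as it varies between participants, through arm, whether they practised, time since practice or individual response.

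**3. Size**

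No figure for M or B is given, so the amount of mixing cannot be computed. The only scale available is the pilot TNF-α fall in section 1: 13.8 − 12.3 = 1.5, and 1.5/13.8 = 10.9%.

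As an illustration only, assume a between-arm difference of 1.5, borrowed from the pilot's change within a group, and an SD of 1.6, the larger of the two pilot SDs. Let a share f of that difference be immediate; the rest is 1.5 × (1 − f). Power is for a two-sided t-test at 0.05, with 30 per arm or with 30 × 0.7 = 21 per arm after the protocol's 30% dropout.

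| f (assumed) | Longer-lasting part | Power, 30 per arm | Power, 21 per arm |
|---|---|---|---|
| 0 | 1.50 | 94.6% | 84.2% |
| 0.25 | 1.125 | 76.4% | 60.4% |
| 0.50 | 0.75 | 43.1% | 31.7% |
| 0.75 | 0.375 | 14.5% | 11.5% |

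The first row is as compatible with the documents as any other. The table shows how the ability to detect the longer-lasting part alone depends on an unknown; it is not an estimate.

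**4. The protocol's own sample size is untouched**

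For PDSS-2, n = 2(1.96 + 0.84)² × 10.7²/11.5² = 13.6, so 14 per group, and 14/0.7 = 20. This agrees with section 5.1 and does not involve the blood samples.

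**The case against.** The strongest reply has five parts.

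- **Same-morning practice is inferred.** No text says that participants practise on a visit morning; travel or non-adherence may prevent it. This stands, and the point is therefore put as likely, not as fact.
- **Aim II does not promise a sustained change.** A reader might infer that it does and that the sampling fails it. Section 2.2 speaks only of changes and reductions after the exercise, so that reading is not supported. What remains is that the schedule cannot say which kind of change was seen.
- **The test is against sham.** An immediate effect of the shared movements should largely cancel where both arms still practise. A residue due to breathing, sounds or meditation is itself an effect of the assigned intervention, so it affects what the contrast means more than whether it is valid. Both statements are right. But breathing is the protocol's own candidate mechanism, and the cancellation depends on sham practice that section 3.2 does not clearly extend past week 12.
- **The immediate effect is speculative.** The introduction gives no timescale, and nothing shows that a 15 to 20 minute session alters cytokines later that morning. This stands; the effect may be zero.
- **Pre-draw instructions may sit in a full protocol or laboratory manual.** If they do, the remedy is only to state the rule here. The point rests on the interaction of two rules that the article does state, not on missing detail alone.

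**Conclusion.** The point holds in a limited form. For adherent participants, the stated practice times and draw window make a same-morning session likely before the post-intervention and 6-month samples and impossible before baseline. An immediate effect of the Qigong-specific components, if present, would be mixed with a longer-lasting one in the between-arm cytokine contrast. Any immediate effect would enter the time effect within arms and, so far as it varies between participants, the Aim III correlations.

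This rests on two assumptions: that participants keep to the morning instruction on visit days, and that one session has some effect still measurable at the draw. The documents support the first indirectly and are silent on the second, so no size can be attached. It would be wrong to conclude that the cytokine results will be artefacts or that the Qigong-versus-sham comparison is invalid; nothing in the documents shows that. Only secondary outcomes (Aims II and III) are exposed; the PDSS-2 primary outcome is not. The change is still worth making before sampling starts, because an unrecorded interval between practice and draw cannot be recovered afterwards.

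**What to change.** In section 4.3, set one pre-draw condition for both arms at all three visits: the sample is taken before that day's session, with the 9 to 11 am window unchanged. Record the date and time of the last session on the sample form. Reconcile sections 3.1 and 3.2 so that it is clear whether practice after week 12 is asked of both arms; which is intended is for the sponsor to state.

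The cost is one sentence in section 4.3, one line in the appointment reminder and one field on the form. The downside is that the session comes later in the day on the two post-baseline visit days. The remedy is also partial: practice on the previous evening still precedes the later draws and not the baseline draw. The interval lengthens and becomes known, but conditions do not become identical to baseline.

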### 2.2. Specific Aims

Specific aim I. To examine the effects of Qigong exercise on non-motor symptoms in PD.

Primary hypothesis: Participants will have greater improvement in sleep quality after Qigong exercise than the participants after sham Qigong exercise.

Secondary hypothesis I: Participants will have greater improvement in cognitive function, fatigue, anxiety, depression, overall non-motor symptoms, and quality of life after Qigong exercise than the participants after sham Qigong exercise.

Specific aim II. To examine changes in inflammatory biomarkers in serum after practicing Qigong exercise.

Secondary hypothesis II: Participants will have greater reduction in levels of inflammatory biomarkers (IL-1β, IL-6, and TNF-α) after Qigong exercise than the participants after sham Qigong exercise.

Specific aim III. To examine relationships between changes in non-motor symptom scores and changes in the inflammatory status in PD after the intervention (both Qigong and sham Qigong).

Secondary hypothesis III: Changes in non-motor symptom scores will significantly correlate with changes in levels of the inflammatory biomarkers.

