## 5. Sample Size Estimation, Statistical Methods, and Reporting Results

### 5.1. Sample Size Estimation

A total of 60 participants will be recruited. The estimation of sample size was based on 80% statistical power regarding one of the primary variables, overall sleep quality (PDSS-2 total score). In our preliminary study, we observed a significant change after Qigong exercise in overall sleep quality by 11.5 points between two groups (experimental vs. control). A pooled standard deviation between two groups was 10.7. With a statistical power of 80% and a Type I error rate at 0.05, the estimated sample size was 14 for each group. Considering a potential dropout rate of 30%, the estimated sample size is 20 for each group. However, this sample size may not have enough statistical power for testing secondary hypotheses related to variables of other non-motor symptoms and/or serum biomarkers. Therefore, we propose to enroll 30 participants in each of the intervention arms.

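### The stated TNF-α detection range starts at 15.6 pg/mL, above the team's own pilot serum means (13.8 falling to 12.3, unit assumed pg/mL); the two figures must be reconciled before any TNF-α assay is run

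*Protocol article*

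**What the plan says.** Section 4.3 (Serum Biomarkers) fixes the TNF-α kit and its working range: "TNF-α (ThermoFisher Scientific, Rockford, IL, USA; detection range 15.6 pg/mL to 1,000 pg/mL". The ranges given there for IL-1β and IL-6 start at 3 pg/mL. On sampling, the same section says: "Venous blood samples will be collected from participants three times, baseline, post-intervention, and 6-month follow-up".

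The Introduction (section 1) gives the pilot result that motivates the biomarker aims, a "significant decrease in serum level of TNF-α from 13.8 ± 0.6 to 12.3 ± 1.6", together with a correlation between TNF-α and sleep quality (R² = 0.62). It prints no unit, does not define ±, and gives neither the number assayed nor the assay used.

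Two hypotheses in section 2.2 depend on this measurement. Secondary hypothesis II begins: "Participants will have greater reduction in levels of inflammatory biomarkers (IL-1β, IL-6, and TNF-α) after Qigong exercise". Secondary hypothesis III is: "Changes in non-motor symptom scores will significantly correlate with changes in levels of the inflammatory biomarkers". Section 5.2 plans to analyse mean changes by mixed-design ANOVA and relationships by correlation coefficients.

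**The concern.** Sections 1 and 4.3 do not fit together for TNF-α. If the pilot values are in pg/mL, the mean before Qigong is already under the kit's stated lower limit, the mean after it is lower still, and the hypothesised direction is downward.

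TNF-α is the only one of the three biomarkers for which the article cites a pilot effect, so it carries most of the empirical case for Aims II and III. If most samples read below range, few participants would have a measurable change. A comparison of mean changes, or a correlation with symptom change, would then say little either way. Section 5.1 partly justifies raising enrolment from 20 to 30 per arm by the power needed for serum biomarkers. More participants do not help when the values lie under the assay's floor.

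**Working it through.** **Inputs.** Lower limit L = 15.6 pg/mL (section 4.3). Pilot TNF-α 13.8 ± 0.6 before and 12.3 ± 1.6 after Qigong (section 1). 30 per arm (section 5.1). Assumed: the pilot unit is pg/mL, values are roughly normal, and the trial population resembles the pilot's.

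**The plan's own figure.** The article has no calculation for TNF-α. Its only sample-size calculation is for PDSS-2: n = 2(1.96 + 0.84)² × (10.7/11.5)² = 13.6, so 14 per group, and 14/(1 − 0.30) = 20. This reproduces the stated 14 and 20 and is untouched by the present point.

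**Distance from the limit.** 15.6 − 13.8 = 1.8 before; 15.6 − 12.3 = 3.3 after. The pilot change is 13.8 − 12.3 = 1.5, so the gap at the post mean is 3.3/1.5 = 2.2 times the pilot change.

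**Share of samples below range.** P(X < L) = Φ((L − mean)/SD). If ± is a standard error, SD = SE × √n with n assumed.

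| Reading of ± | SD before / after | z before / after | Below 15.6 before / after |
|---|---|---|---|
| SD | 0.60 / 1.60 | 3.00 / 2.06 | 99.9% / 98.0% |
| SE, n = 5 | 1.34 / 3.58 | 1.34 / 0.92 | 91% / 82% |
| SE, n = 10 | 1.90 / 5.06 | 0.95 / 0.65 | 83% / 74% |
| SE, n = 15 | 2.32 / 6.20 | 0.77 / 0.53 | 78% / 70% |

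Because both means lie under L, any symmetric distribution puts more than half of the samples below range.

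**Effect on the between-arm comparison.** A simulation (4,000 runs, 30 per arm, control assumed unchanged at 13.8 with its baseline spread, within-person correlation 0 or 0.5) compared a t-test on change using all true values with the same test after setting values below 15.6 to 15.6. That substitution is illustrative; the article states no rule.

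- ± as SD: power is 99% or more with all values known and about 0% after substitution. The expected number of Qigong participants measurable at both visits is about 0 of 30.
- ± as SE, n = 5: 49–65% with all values known, 20–26% after substitution.
- ± as SE, n = 10: 26–38% with all values known, 31–39% after substitution.

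The rejections after substitution in the SE cases do not support the hypothesis. After substitution the mean exceeds 15.6 by SD·φ(z) − (L − mean)(1 − Φ(z)). For n = 10 this is 5.06 × 0.323 − 3.3 × 0.257 ≈ 0.78 for Qigong after treatment, and 1.90 × 0.254 − 1.8 × 0.171 ≈ 0.17 for control. The arm with the lower true mean appears higher, because only its wider upper tail is seen.

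**How low a limit would be enough.** Mean minus two spreads after Qigong is 12.3 − 2 × 1.6 = 9.1, which might suggest about 9 pg/mL. If ± is an SD, Φ((9 − 12.3)/1.6) = 2% of post values fall below 9. If ± is an SE, Φ(−3.3/3.58) = 18% (n = 5) to Φ(−3.3/6.20) = 30% (n = 15) do. The target therefore cannot be set from the printed summary.

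**The case against.** The strongest reply is that the pilot did obtain numbers in this range: two means, a significant fall and a correlation with sleep. The article does not say which assay gave them. The pilot may have used another kit, values may have been read below the nominal range, or the printed range may be wrong (for example, the span of the standard curve and not the kit's sensitivity). In the last case the repair is one corrected number. This stands, and it limits the finding to an inconsistency that has to be resolved.

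The missing unit and the undefined ± also stand, so the result is conditional. A different unit does not clearly rescue the plan, however. Read as ng/mL, 13.8 would be 13,800 pg/mL, above the 1,000 pg/mL upper limit, and section 4.3 mentions no dilution. Trial participants could have higher TNF-α than the pilot's, but no figure in the article suggests it.

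A reader might infer that the TNF-α hypothesis simply cannot be tested, or that any null result would be an assay artefact. The article does not support that. Under the SE readings above, 9–22% of baseline and 18–30% of post values would be measurable: a small and selected subset, but not none. A reader might also extend the problem to IL-1β and IL-6; no pilot values are given for them, so nothing shows that their 3 pg/mL limits are too high.

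Finally, a rule for values below the limit is commonly left to an analysis plan that is not shown here. Its absence is not part of this point.

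**Conclusion.** The inconsistency between sections 1 and 4.3 is real, and nothing else in the article resolves it. On a pg/mL reading, with a roughly normal distribution, a correctly stated range and a population like the pilot's, most TNF-α samples would be below range: 98–99.9% if ± is an SD, and about 70–91% if it is an SE from an assumed 5 to 15 participants. The TNF-α components of Secondary hypotheses II and III would then be uninformative.

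The damage is confined to one of three biomarkers in secondary hypotheses. The primary hypothesis and the sample-size calculation are not affected. Severity: should be fixed, before the serum is assayed.

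**What to change.** Before any TNF-α assay is run, reconcile the two sections and state the unit, the meaning of ±, the number assayed and the assay for the pilot figures. Then do one of the following:

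1. If the kit's true lower limit is below 15.6 pg/mL, correct the range in section 4.3 and confirm that the corrected limit lies well below the pilot values.
2. If 15.6 pg/mL is right, use a TNF-α assay whose lower limit lies well below the pilot distribution. Set that limit from the pilot's individual values; about 9 pg/mL is low enough only if ± is an SD.

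If a material share of values still falls below the limit, analyse TNF-α as left-censored or by a rank method in place of the planned mean-based ANOVA.

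Cost: correcting the range is a text change. A more sensitive kit may be dearer (the article gives no prices), and a censored or rank analysis over three time points takes some extra statistical work. No extra visits or blood are needed, since section 4.3 already plans to freeze serum aliquots until assay.
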